### Intervention regimes and supplement preparation

Two hundred seven eligible equol-non-producers of post-menopausal women who have completed a 2-week run-in period will be randomized to either one of the 3 groups; placebo group, low-equol group (10 mg/d) and high equol group (20 mg/d).

**Table Taba:** 

Groups	Supplementations			Sample size	Duration
	S-equol	Starch	soy flour		
Placebo	0	20 mg	10 g	69	6-month
Low-equol	10 mg	10 mg	10 g	69	6-month
High-equol	20 mg	0	10 g	69	6-month

The dose of natural S-equol used in the present study is determined mainly on previous studies. A 10 mg natural S-equol is reported to be effective for improving menopausal symptoms [41] and bone turnover [40] with no observed side effect. A higher dose of 30 mg/d for 12-week [42] or even 160 mg/d for 14-day [50] in previous pilot studies did not reveal any serious adverse events except for one woman developing a rash [42]. The safety of S-equol has been confirmed in genotoxicity [51], acute and subchronic toxicity [52], and reproductive and development toxicity tests [53].

In order to obtain good blinding effect and improve supplement solubility in water, 10 g soy flour will be included in all 3 groups. Our previous trials have shown soy product was more acceptable to mid-life women than milk powder. Starch will be added to supplements to make 3 groups of packets with similar weight. The natural S-equol will be purchased from Otsuka Pharmaceutical Co. Ltd (Japan). The supplements of 3 groups will be processed by a local GMP certified pharmaceutical company. Daily dosage will be filled into identical looking packets. The supplements will be delivered to subjects every four weeks.

Supplement will be suggested to be mixed with 100 ml of water, juice, milk or adding to soft foods such as oatmeal and intake daily before breakfast. Subjects will be asked to maintain their usual level of physical activity, discontinue the use of other dietary and herbal supplements (i.e., dietary fiber, minerals, Vitamin C and E, fish oils, flavonoids etc.) known to influence BP, minimize the intake of soy foods (≤2 servings per week), refrain from high salt diet and restrict alcohol intake (≤2 drinks per week).

### Run-in exercise

Prior to the study proper, a 2-week run-in exercise with the use of placebo supplement (20 mg starch + 10 mg soy flour), will be carried out to familiarize the subjects with the trial requirements. Subjects who consume ≥90 % of supplements provided and without any side-effects will be formally enrolled into the study.

### Randomization procedures

A block randomization will be used for subject allocation. 207 continuous serial numbers (1–207) will be divided into 23 blocks with a block size 9. In each block, three treatments will be randomly allocated for each serial number based on the sequence of computer generated random numbers by SPSS (Release 16, SPSS Inc., Chicago, USA). The 207 serial numbers will be labeled on the corresponding supplements. Each serial number will correspond to one of three treatments. The supplements will be assigned to participants according to the sequence of their visits after the completion of the run-in period. Three treatments will then be randomly allocated to the three groups.

### Blinding and code breaking procedures

The three identical looking supplements will be labeled with a serial number by a co-investigator who is not responsible for subject contact and assessment. Participants, investigators and laboratory technicians will be blinded to the treatment assignment until the conclusion of the trial. The principal investigator will be responsible for breaking the randomization code after the completion of data analyses or in emergency situations. Intensive effort will be undertaken to locate a subject who fail to attend for follow-up interview or examination. Reason for non-completion or termination will be documented.

## Data collection

Twenty-four hours ABP, vascular function, overnight fasting (10–12 h) venous blood samples and 24-hour urine samples will be measured or collected at baseline and at 24 weeks after treatment. Plasma/serum will be isolated within 2 h after collection. Specimens will be stored at −80 °C till analyses. All samples from each subject will be run in the same assay/batch to avoid inter-assay variability. Structured questionnaire interview and anthropometric measurements will be administered at baseline and at 24 weeks. Habitual dietary intakes will be evaluated by a validated food frequency questionnaire and habitual physical activity by Modified Baecke questionnaire validated in Hong Kong population. Urinary analysis for sodium, potassium, and creatinine will be tested by Hitachi 917 autoanalyzer, Roche Diagnostics.

### Primary outcome measures—24-hour ambulatory BP

All arterial parameters will be measured at baseline and 24 weeks by an experienced research assistant. Participants will be asked to fast for 8 h and withhold vasoactive medications, alcohol, and caffeine for 12 h before the study visit.

### 24-hour ambulatory BP

Twenty-four hours ABP will be measured with ABP Monitor (TM2430, A&D Company, Limited, Japan) based on a standard protocol [54]. Participants will be fitted with an ABP monitor by a trained investigator, with the cuff attached to the non-dominant upper arm for the entire 24-hour period. The measurements will be carried out every 30 min during the daytime (from 06:00 a.m. to 12:00 p.m.) and 60 min during the night (1:00 a.m. to 06:00 a.m.), providing at least 40 valid readings of BP throughout the 24-hour. Participants will be received verbal and written instructions on the monitors and complete a diary to record sleep, medication, posture activity and symptoms. A series of calibration readings will be taken with a mercury sphygmomanometer (within 5 mm Hg of the mercury readings). The mean values of SBP and DBP in all day will be calculated by the device-specific software.

### Secondary outcome measures- vascular function

#### Brachial endothelial function by flow mediated dilation (FMD)

Vascular endothelial function will be assessed with high-resolution ultrasound (SIMENS, ACUSON S2000) on the brachial artery during reactive hyperemia by standard methodology [55]. Ischemia is induced with a suprasystolic pressure cuff around the upper portion of the arm. After exactly 5 min of occlusion, reactive hyperemia will ensue and the peak brachial artery diameter will be measured between 45 and 75 s. Percentage FMD is defined as the difference between the maximal brachial artery diameter during reactive hyperemia and the baseline divided by the baseline brachial artery diameter.

#### Arterial stiffness and stenosis by pulse wave analysis (PWA)

PWA will be performed by a dedicated tonometry system (VP-2000; Omron Healthcare, Inc. Bannockburn, Illinois, USA), following a standardized procedure [56]. Patients will be fitted with sphygmomanometer cuffs on both arms and legs and a carotid artery pressure sensor on the neck. Pulse wave velocity (PWV) will be determined from recorded pressure wave forms over both the brachial-ankle and the heart-ankle arterial segments, which are derived from computer generated pulse transit times and measured distances between the two recording sites. Ankle brachial index (ABI) is the ratio of SBP of ankle to brachial reflecting lower-extremity arterial stenosis.

### Tertiary outcomes

#### Biomarkers for endothelial function and inflammation

Serum endothelin-1 (ET-1), soluble vascular cell adhesion molecule–1 (VCAM-1), soluble intercellular adhesion molecule–1 (ICAM-1) and E-selectin will be measured by commercial ELISA kits. Serum C-reactive protein (CRP) will be measured with a validated high sensitivity immunoturbidimetric assay.

### Other cardiovascular risk markers

Anthropometric measurements, plasma lipids profile and fasting glucose will be conducted at baseline and 6-month. Height, weight, waist and hip circumference, body fat percentage will be measured by standardized procedure. Body mass index (BMI), and waist to hip ratio (WHR) will be calculated. Serum/plasma glucose, triglyceride, total cholesterol, HDL and LDL cholesterol will be analyzed (Hitachi 917 auto-analyzer, Roche Diagnostics).

### Assessment of compliance

Compliance will be assessed by counting the returned supplements and estimation of percentage of intake, as well as urinary excretion of isoflavones at baseline and 24 weeks. Urinary isoflavones including daidzein and equol will be determined by high performance liquid chromatography (HPLC).

### Statistical analysis

Relevant parametric and non-parametric tests will be used for testing the differences in the baseline characteristics and outcomes of post treatment among the three study groups. The major approach of analysis will be one way analysis of variance (ANOVA) to compare the change and percentage change of outcomes at 24 weeks among the three groups. Analysis of covariance will also be made to examine if the results are similar after adjusting for potential confounders. The primary analysis will be an intention to treat (ITT) analysis that included all subjects who are randomized. A secondary per protocol analysis will be performed including subjects with good compliance (defined as subjects who consumed ≥ 80 % of provided supplements or with urinary isoflavones level above predefined values for valid users). The non-compliant subjects will be described and compared to the compliant subjects. Dose-dependent effects will be evaluated with the Jonckheere’s trend test. The Bonferroni test will be used for post hoc multiple comparisons among the three groups. The primary outcome variables of 24 h ambulatory BP (mean SBP and mean DBP in all day) will be tested at a significance level of 2.5 % in order to maintain an overall 5 % level. The two important secondary outcomes for assessment of vascular function (%FMD and PWV) will be tested at a significant level of 1.25 %. Exploratory analyses will be used to test each of the tertiary outcomes at the 5 % significance level. Further stratification analysis will be conducted to examine if the effects differed across subgroups such as years since menopause and BMI etc.

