### Sample size planning

Our previous RCT [47] on soy showed a 4.2 mmHg net reduction (SD of change 10 mmHg) in SBP after 6-month soy protein and isoflavones supplementation relative to placebo group among 130 pre- and hypertensive postmenopausal women [48]. Assuming a reduction of 5 mmHg of treatment effect on SBP (main effect), 63 subjects per group will yield a power of at least 80 % at 5 % level of significance (for a 2-side t-test). Allowing for 10 % non-compliance or drop out from the study, 69 subjects per group and a total 207 subjects (63 × 3 × 110 %) will be recruited. Similar attrition rates (7.8 % and 7.0 %) have been reported in our previous soy trials [45, 49].

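### %FMD is already a ratio with no positive floor, yet it is also to be analysed as a percentage change, and the plan does not say which scale carries its 1.25% test

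*Protocol article*

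**What the plan says.** Under Statistical analysis, the major approach is "one way analysis of variance (ANOVA) to compare the change and percentage change of outcomes at 24 weeks among the three groups". The sentence names two scales, ranks neither, and exempts no outcome.

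The same section gives %FMD formal status: "The two important secondary outcomes for assessment of vascular function (%FMD and PWV) will be tested at a significant level of 1.25" per cent. It does not say whether that test is made on the change or on the percentage change. A covariate analysis is planned only as a check: "Analysis of covariance will also be made to examine if the results are similar after adjusting for potential confounders". Baseline %FMD is not named as a covariate.

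The section on brachial endothelial function defines the measure as "the difference between the maximal brachial artery diameter during reactive hyperemia and the baseline divided by the baseline brachial artery diameter". The outcome is thus already a within-visit percentage. The article gives no mean, SD, distribution, effect size or power for it.

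**The concern.** A percentage change is a sound summary only if the baseline is safely above zero. Nothing in the definition of %FMD ensures that. Its numerator is the difference between two measured diameters, with the peak read in a fixed window after cuff release, so an artery that hardly dilates can give a value near zero or, through measurement error, below it. The Background links hypertension with endothelial dysfunction, and no eligibility criterion sets a minimum FMD.

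Read as written, the plan takes a percentage of a percentage for a formally tested secondary outcome. At stake are:

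- a result that a few women with very small baselines can dominate;
- improvements scored as deteriorations when the baseline is negative;
- a randomised woman with a zero baseline who has no value in an analysis meant to include everyone randomised;
- two results for one 1.25% allocation, with no rule for which one counts.

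**Working it through.** **1. The plan's own figure.** Sample size planning gives a 5 mmHg effect, an SD of change of 10 mmHg, two-sided 5%, 80% power and 63 per group.

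n = 2 × (1.960 + 0.842)² × 10² / 5² = 62.8, rounded up to 63.

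Power at 63 is 80.1% by the normal approximation and 79.5% by the exact t-test, so the figure reproduces. It concerns SBP only. There is no corresponding figure for %FMD.

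**2. The same gain on the percentage scale.** Percentage change = 100 × (week 24 − baseline) / baseline.

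| Baseline %FMD | Week 24 | Absolute change | Percentage change |
|---|---|---|---|
| 6.0 | 8.0 | +2.0 | 2.0/6.0 = +33% |
| 0.5 | 2.5 | +2.0 | 2.0/0.5 = +400% |
| −0.5 | 1.5 | +2.0 | 2.0/(−0.5) = −400% |
| 0 | 2.0 | +2.0 | undefined |

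This step needs no assumption beyond the definition.

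**3. Power on each scale.** From the article: 63 per arm, three arms, alpha 1.25%. Assumed: true gains of 0, 1 and 2 %FMD points, correlation 0.5 between visits, and the baseline means, SDs and shapes shown. Cells are the power of one-way ANOVA on percentage change, from 1,000 simulated trials each.

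| Baseline mean ± SD | Normal | Gamma | Lognormal |
|---|---|---|---|
| 5 ± 3 | 1% | 57% | 84% |
| 6 ± 3 | 3% | 66% | 85% |
| 8 ± 3 | 18% | 73% | 81% |
| 8 ± 2.5 | 51% | 88% | 94% |

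Absolute change gave 79-96% throughout. A separate run of the same design gave 1-54%, 55-91% and 83-93% for the three shapes, against 77-96% on absolute change. The ranges therefore move by a few points between runs, and the lower lognormal end is best read as about 80%.

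Under normal baselines of 6 ± 3, about 4 of 189 women have a percentage change of the wrong sign. In 27% of those trials the mean percentage change for high dose minus placebo points the wrong way. With gamma or lognormal baselines this happens in fewer than 1% of trials.

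**4. A second set of assumptions.** Here the high-dose gain is 0.65 SD of the change, which gives absolute change 77-80% power. Under normal baselines, percentage-change power depends on the baseline coefficient of variation (CV = SD/mean):

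- CV 0.5-0.6: 1.5-4.3%
- CV 0.43: 7-9%
- CV 0.31: 38-40%
- CV 0.25: 58-62%
- CV 0.15-0.20: 69-74%

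Under lognormal baselines it is 79-89%, so nothing is lost.

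**5. Gain from baseline adjustment.** With equal SDs at both visits, the variance of the change is 2 × SD² × (1 − r), and the ANCOVA residual variance is SD² × (1 − r²). At r = 0.5 the ratio is 0.75/1.00 = 0.75. In the step 3 scenarios, ANCOVA on the absolute scale raised power from 77-96% to 89-99%.

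**6. Contrast with SBP.** Table 1 gives SBP 135.1 ± 16.6, so zero lies 135.1/16.6 = 8.1 SDs below the mean. With an SD of change of 10 mmHg, a high-dose effect of 0.65 × 10 = 6.5 mmHg and alpha 2.5%, power was 84% on change and 85% on percentage change. The difficulty does not arise for SBP.

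**The case against.** A reader might infer that the key secondary test loses most of its power. The article does not support that. Absolute change is planned in the same sentence and keeps its power, and nothing makes percentage change the deciding scale. The loss affects the formal test only if percentage change is chosen to carry it.

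A reader might also infer that negative baselines will occur and that the loss will be nearly total. That is not documented either. The counts of wrong-signed women belong to an assumed normal curve. %FMD uses a maximal diameter, which pushes values upward, and the exclusion criteria remove regular smokers and women with stroke or cardiac infarction. With strictly positive baselines the loss runs from moderate to none. These points stand, and they limit the size of the finding.

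Non-parametric tests and Jonckheere's trend test are also planned. Under the worst normal case (5 ± 3), applied to percentage change, Jonckheere keeps 66% power and Kruskal-Wallis 53%, against 1% for ANOVA. Ranks thus curb the influence of tiny baselines. They do not correct a reversed sign or define a value at zero.

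Finally, a condensed article may leave the choice of scale to an analysis plan. That would answer a mere omission. Here the article states a positive rule, percentage change of outcomes without exception, and a later plan would inherit it. Having two unranked scales is common to all outcomes, but for SBP they give nearly the same power, so it matters far less there.

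**Conclusion.** The point holds in a limited form. The stated rule yields, for one formally tested secondary outcome, a quantity that is unstable near zero, undefined at zero and wrong in sign below it. It also leaves open whether that quantity or the absolute change carries the 1.25% test. This much follows from the definition and the analysis rule alone.

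The effect on power cannot be fixed from the article. It ranges from almost total loss in the percentage-change ANOVA, if baselines are roughly normal with a CV of about 0.43 or more, to no material loss if they are lognormal. All these figures rest on assumed %FMD means, SDs, correlations, shapes and gains. The absolute-change analysis is sound in every scenario.

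**What to change.** In Statistical analysis, state that %FMD is tested once at the 1.25% level, as the absolute change in %FMD points from baseline to 24 weeks, by ANCOVA with baseline %FMD as covariate. State also that no percentage change of %FMD will be analysed.

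This costs one sentence, written before unblinding. Baseline %FMD is already collected, so no new data or participants are needed. The only loss is a relative-change figure for %FMD.

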**Methods/design:**

This will be a 6-month double-blind, randomized, placebo-controlled trial among 207 non-equol producing postmenopausal women with prehypertension or early untreated hypertension. Eligible participants who have completed a 2-week run-in will be randomized to either one of the 3 groups: placebo group, low-equol group (10 mg/d) and high equol group (20 mg/d). The outcome measures will be conducted at baseline and at the end of the trial including 24 h ambulatory BP, endothelial function (by ultrasound determined brachial flow mediated dilation), arterial stiffness (by pulse wave analysis) and other cardiovascular risk factors (lipid profile, glycemic control and inflammatory biomarkers). Urinary isoflavones will be tested for compliance assessment. One way analysis of variance will be applied to compare the 6-month changes in ambulatory BP or parameters of vascular function among the 3 treatment groups.

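### The main analysis is an unadjusted ANOVA on two unranked scales; a baseline-adjusted ANCOVA on one scale would be more precise and needs no new data

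*Protocol article*

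**What the plan says.** The Statistical analysis section of the protocol article gives as its main method "one way analysis of variance (ANOVA) to compare the change and percentage change of outcomes at 24 weeks". Neither of the two scales is placed first. The abstract is narrower: "One way analysis of variance will be applied to compare the 6-month changes in ambulatory BP", with no mention of percentage change.

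Covariate adjustment appears once: "Analysis of covariance will also be made to examine if the results are similar after adjusting for potential confounders". That gives ANCOVA a supporting role, and the baseline value of the outcome is not named among the covariates.

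The same section tests each of the two primary variables, 24-hour mean SBP and mean DBP, at 2.5%. The Data collection section schedules ambulatory blood pressure at baseline and at 24 weeks only.

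Sample size planning works on absolute change: "Assuming a reduction of 5 mmHg of treatment effect on SBP (main effect"), with "SD of change 10 mmHg" and a 5% "level of significance (for a 2-side t-test"), giving 63 women per group, or 69 per group and 207 in all after an allowance for non-compliance or drop-out.

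**The concern.** Two choices are fixed less well than they could be.

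First, the trial collects the covariate that usually says most about the outcome, the same woman's baseline ambulatory pressure, and the main test uses it only by subtracting it. Subtraction forces a slope of one on baseline. ANCOVA estimates the slope, and where the true slope is below one its residual variance is smaller.

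Second, 2.5% is allotted to each of SBP and DBP, but each can be tested as absolute change and as percentage change. If the two p-values fall on opposite sides of 0.025, the text does not say which one is the result.

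At stake are power that could be had without recruiting anyone, and a primary result that can be identified before unblinding.

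**Working it through.** **Inputs from the article**
- Effect 5 mmHg, SD of change 10 mmHg, two-sided 5%, 63 per group (Sample size planning).
- 2.5% for each primary variable (Statistical analysis).
- SBP SD 16.6 mmHg around a mean of 135.1 mmHg in the 292 screened women (Table 1), not identified as ambulatory.

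**Input that must be assumed**
- The correlation rho between baseline and 24-week pressure, which the article does not give.

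**1. The plan's own figure.** The normal-approximation formula for two means (difference 5, SD 10, two-sided 5%, 80% power) gives 63 per group, with power 80.1%. The exact noncentral t gives 79.5% at 63. The stated size reproduces.

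**2. Variance formulas.** Let s be the common SD at both visits.
- Change score: 2s²(1 − rho)
- ANCOVA residual: s²(1 − rho²)
- Ratio ANCOVA/change: (1 + rho)/2, so the reduction is (1 − rho)/2

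**3. Values of rho.** With SD of change 10, 100 = 2s²(1 − rho), so rho = 1 − 100/(2s²).
- s = 16.6: 1 − 100/551.12 = 0.82
- s = 12 (assumed): 1 − 100/288 = 0.65
- s = 10 (assumed): 1 − 100/200 = 0.50

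**4. Gain.** Residual SD = 10 × √((1 + rho)/2). Power is for a two-group comparison of 5 mmHg, 63 per group, two-sided 2.5%, noncentral t.

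| Analysis | Variance reduction | Residual SD | Power at 2.5% |
|---|---|---|---|
| Change score | – | 10.00 | 70.4% |
| ANCOVA, rho 0.90 | 5% | 9.75 | 72.9% |
| ANCOVA, rho 0.82 | 9% | 9.54 | 74.9% |
| ANCOVA, rho 0.65 | 17% | 9.09 | 79.2% |
| ANCOVA, rho 0.50 | 25% | 8.66 | 83.3% |
| ANCOVA, rho 0.30 | 35% | 8.06 | 88.6% |

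A simulation with 69 per arm and 10% of 24-week values missing at random gave variance reductions of 8.3% (rho 0.82) and 24.7% (rho 0.50), in line with the formula.

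**5. Unequal SDs.** Keep baseline SD s₀ = 16.6 and SD of change 10, and let the 24-week SD s₁ vary. Then cov = (s₀² + s₁² − 100)/2, and the ANCOVA variance is s₁² − cov²/s₀².
- s₁ = 14: cov = 185.78; 196 − 125.25 = 70.75, a reduction of 29%.
- s₁ = 18.5: cov = 258.91; 342.25 − 243.26 = 98.99, a reduction of 1%.

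**6. The three-group test.** The planned test is an omnibus F, with noncentrality 63 × Σ(μ − mean)²/SD². At 2.5% with SD 10:
- Mean changes 0/−5/−5: 63 × 16.67/100 = 10.5, power 75%.
- Mean changes 0/−2.5/−5: 63 × 12.5/100 = 7.9, power 60%.

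Adjustment divides the noncentrality by (1 + rho)/2, so it raises these as well. For a pairwise test with a further Bonferroni division by three (0.025/3), power goes from 55% unadjusted to 60% (rho 0.82) or 71% (rho 0.50).

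**7. Cost.** One baseline slope takes one of 3 × 63 − 3 = 186 residual degrees of freedom.

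**The case against.** The strongest reply is that nothing here is an error. Randomisation makes the between-arm difference in mean change unbiased, the analysis matches the SD of change used for sample size, and ANCOVA is already planned. The phrase about confounders does not exclude the baseline value, and covariate lists are often left to the SAP. The abstract and the mmHg-based sample size both point to absolute change. Most of this stands, and it sets the size of the point: this is a matter of efficiency and clarity. It does not remove the point, because the article itself gives the decisive role to the unadjusted test and names percentage change beside absolute change without ranking them.

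It is also fair that the gain is conditional. The 16.6 mmHg comes from a screening pool, the SD of 10 comes from another trial, and equal SDs are assumed. The 70% and 75–83% describe a pairwise t-test, not the three-group F test or the Bonferroni comparisons.

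A reader might infer more than the documents support:
- **That ANCOVA would satisfy the intention-to-treat statement where ANOVA does not.** The article says: "The primary analysis will be an intention to treat (ITT) analysis that included all subjects who are randomized". With a single post-baseline measurement, a woman without a 24-week value leaves an ordinary ANCOVA exactly as she leaves an ANOVA of change. Handling of missing values may sit in the full protocol or SAP.
- **That regression to the mean biases the comparison.** It acts equally on all arms in expectation; only chance baseline imbalance remains.
- **That percentage change of %FMD is unstable.** The article gives no baseline FMD value to show it, and FMD is a secondary outcome.
- **That choosing ANOVA causes the shortfall from 80% power.** The fall from 79.5% to 70.4% comes from sizing at 5% and testing at 2.5%, which is a separate matter.

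**Conclusion.** The point holds as one of precision and of an unranked second scale, not of bias. Assuming equal SDs at both visits, baseline adjustment reduces the variance of a treatment difference by about 9% to 25% for rho between 0.82 and 0.50, and by 5% to 35% for rho between 0.9 and 0.3. With unequal SDs the reduction ran from 1% to 29% in the two cases tried. Under the equal-SD assumption, pairwise power for 5 mmHg at 2.5% with 63 per group goes from about 70% to between 75% and 83%. The direction is secure, since with equal SDs the ratio (1 + rho)/2 is below one for any rho below one. The exact size cannot be fixed from the article.

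The two-scale problem is chiefly one of ambiguity. For SBP the baseline varies by only about 12% of its mean (16.6/135.1), so the two scales should usually agree, but the plan should still say which one decides.

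**What to change.** For each of 24-hour mean SBP and mean DBP, name one decisive test at 2.5%: ANCOVA of the 24-week value (or, equivalently for the treatment effect, the absolute change) on treatment arm, with the baseline value of the same variable as covariate. State that any further covariates are measured at baseline, and list them before unblinding. Report percentage change as descriptive, and keep the unadjusted ANOVA of change as a supportive analysis if wanted.

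This changes wording in the protocol and SAP and uses one degree of freedom. It needs no new data, visits or participants. How women without a 24-week reading are handled should be stated separately, because this change does not settle it.

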## Method/design

This study will be a 6-month double-blind, randomized, placebo-controlled trial with three intervention arms.

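### With only three groups, the Bonferroni division after a significant ANOVA is valid but unnecessary; a written closed procedure gains about 4 to 10 points of power for high dose versus placebo

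*Protocol article*

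**What the plan says.** The Method/design section describes a "randomized, placebo-controlled trial with three intervention arms": placebo, low equol and high equol. Under Statistical analysis, one-way ANOVA of the changes at 24 weeks is the main approach. Mean 24-hour SBP and mean 24-hour DBP "will be tested at a significance level of 2.5 % in order to maintain an overall 5 % level"; %FMD and PWV are assigned 1.25%, and tertiary outcomes 5%. For the pairs, the section says only: "The Bonferroni test will be used for post hoc multiple comparisons among the three groups".

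Two things are left unsaid. The words post hoc imply that the pairs follow the ANOVA, but the text does not say they are tested only if the ANOVA is significant. It also gives no level per pair; 0.025/3 = 0.83% is the natural reading for a primary variable. The Bonferroni sentence is not limited to the primary outcomes.

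Sample size planning takes its variability from an earlier soy trial with a "4.2 mmHg net reduction (SD of change 10 mmHg) in SBP", and continues: "Assuming a reduction of 5 mmHg of treatment effect on SBP (main effect"). From this it concludes that "63 subjects per group will yield a power of at least 80" percent, for a two-sided t-test at 5%.

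**The concern.** The hypotheses are that equol lowers blood pressure and that the higher dose does more. The pairwise comparisons therefore carry much of the message. If they come after a 2.5% ANOVA, the ANOVA already protects against the case in which all three means are equal. That is the only configuration in which more than one pairwise null can be true, since any two pairwise equalities imply the third. Dividing by three then buys protection that three groups do not need.

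The cost is power for naming an effective dose. The trial was sized for a single two-group test at 5%, so the pairwise tests start below the stated 80% before the further division is applied.

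**Working it through.** **Inputs.** Sample size planning gives a difference of 5 mmHg, an SD of change of 10 mmHg and 63 evaluable per group. Statistical analysis gives 2.5% per primary variable. Three groups give three pairs. The low-dose effect is not stated, so it is varied.

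**1. The plan's own figure.** n = 2(1.960 + 0.842)² × 10²/5² = 62.8, so 63 per group. Power with 63 is 80.1% by the normal approximation and 79.5% by the noncentral t. The stated figure reproduces.

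**2. Why three groups are special.**
- All means equal: a pair can be declared different only if the ANOVA is significant, which happens in 2.5% of trials.
- Exactly two means equal: one true pairwise null remains, and it is tested at 2.5%.
- All means different: no false rejection is possible.

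So ANOVA at 2.5%, then each pair at 2.5%, controls familywise error at 2.5% in every case. With four or more groups the argument fails.

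**3. What the division costs on the mmHg scale.** The standard error of a pairwise difference is 10 × √(2/63) = 1.782 mmHg, with 3 × 62 = 186 degrees of freedom.
- Pair at 2.5%: critical t 2.260, so the observed difference must exceed 2.260 × 1.782 = 4.03 mmHg.
- Pair at 0.83%: critical t 2.667, so it must exceed 2.667 × 1.782 = 4.75 mmHg.

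**4. Simulation.** 1,000,000 trials per scenario, normal changes, equal variances, pooled-variance tests, 63 per group, SD 10, ANOVA at 2.5% first.

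Familywise error for one primary variable:

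| Truth | ANOVA, then Bonferroni | ANOVA, then pairs at 2.5% | Pairs at 2.5%, no ANOVA gate |
|---|---|---|---|
| All means equal | 2.1% | 2.5% | 6.4% |
| One pair equal | 0.8% | at most 2.5% | 2.5% |

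Power (reductions in mmHg for placebo/low/high; left figure is ANOVA then Bonferroni, right figure is the closed procedure):

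| Scenario | High v placebo | Low v placebo |
|---|---|---|
| 0/2.5/5 | 54.7% to 58.6% | 10.5% to 18.8% |
| 0/3/5 | 54.7% to 59.0% | 16.6% to 26.7% |
| 0/4/5 | 54.9% to 61.7% | 33.8% to 45.8% |
| 0/5/5 | 55.2% to 65.4% | 55.3% to 65.4% |
| 0/0/5 | 55.3% to 65.5% | null pair |

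Under 0/5/5, both doses beat placebo in 39% of trials with Bonferroni and 56% with the closed procedure. With all 69 per group analysed, the gain for high dose under 0/5/5 is again about 10 points (60.5% to 70.5%).

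**5. Significant ANOVA but neither dose better than placebo.** With Bonferroni this occurs in 3.9% (0/2.5/5), 3.3% (0/3/5), 3.4% (0/4/5) and 3.3% (0/5/5) of trials. Under 0/0/5 it is 19%, against 8% with the closed procedure.

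**The case against.** **Bonferroni is a standard and valid choice.** This stands. A reader might infer that the planned test has the wrong error rate; it does not. The point is lost efficiency only.

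**The gate is inferred.** This also stands. If the Bonferroni pairs were meant to be tested regardless of the ANOVA, nothing is paid twice. Yet power hardly changes: ungated Bonferroni gives about 56% for high dose versus placebo. The closed procedure still gains 2.9 points under 0/2.5/5 and about 10 under 0/5/5.

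**The 10-point gain needs special scenarios.** Correct. It requires an inert low dose or one equal to the high dose, whereas the study hypotheses predict a graded response. For that case, 4 to 7 points is the fair figure for high dose versus placebo. Low dose versus placebo gains about 8 to 12 points there.

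**A significant ANOVA with no effective dose is rare.** Mostly true: 3 to 4% of trials except when the low dose is inert. It should not be presented as a likely outcome.

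**Other procedures might do better.** The omnibus gate itself costs power: under 0/2.5/5, one ungated test of high dose at 2.5% has about 71%, against 59% with the gate. But using that level ungated for all three pairs gives 6.4% error. The closed procedure is an improvement that keeps the plan's ANOVA and its three pairs; it is not claimed to be optimal.

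**Bonferroni intervals are simultaneous.** True, and this is the real price. Under 0/2.5/5, about 14% of trials would have a non-significant ANOVA with at least one unadjusted 97.5% interval excluding zero. The fix has to deal with this.

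**Conclusion.** The point holds as an efficiency improvement. After an ANOVA significant at the same level, the division by three is unnecessary in a three-group trial. The closed procedure declares every pair that ANOVA followed by Bonferroni would declare, and more, with familywise error still at or below 2.5% per primary variable. For high dose versus placebo the gain is about 4 to 7 points under graded effects and about 10 if the low dose is inert or equals the high dose.

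This rests on a 5 mmHg high-dose effect, SD 10, 63 evaluable per group, roughly normal changes with equal variances, an assumed range of low-dose effects, and a gate that the protocol implies but does not state.

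A reader might infer that the change repairs the trial's power. It does not: power for high dose versus placebo stays at about 59 to 65%, because the sample size was computed at 5% for one two-group comparison while the analysis works at 2.5% behind a three-group test. That is a separate and larger matter.

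**What to change.** Replace the Bonferroni sentence with one that covers all outcomes and states the gate:

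> *For each outcome, pairwise comparisons will be tested only if the overall three-group ANOVA is significant at that outcome's level (2.5% for each primary BP variable, 1.25% for %FMD and PWV, 5% for tertiary outcomes); each pair is then tested at that same level using the pooled variance (closed procedure for three groups).*

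Add that pairwise confidence intervals are not adjusted for multiplicity and will not be used to claim significance when the ANOVA is not significant.

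The gate is essential: dropping Bonferroni without it would raise familywise error to about 6.4% per primary variable. The cost is two sentences and the loss of simultaneous intervals, with no extra participants or measurements. The rule should be fixed before unblinding, and it would have to be reconsidered if the number of groups changed.
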